**Methods:**

CLINCH is an investigator led, academic driven multicenter, prospective, randomized, open-label, blinded endpoint (PROBE) phase IV pilot study evaluating cerebrolysin in primary lobar ICH. We will randomize 88 patients with lobar ICH (30–80 mL; GCS 8–15; National Institutes of Health Stroke Scale, NIHSS ≥8) within 6 h of onset in a 1:1 ratio to receive either intravenous cerebrolysin (50 mL daily for 14 days) plus standard care including intensive rehabilitation, or standard care alone. Randomization will be stratified by ICH volume (30–50 vs. 51–80 mL) and GCS (8–12 vs. 13–15). Primary endpoints include 90-day mortality (safety) and functional independence (modified Rankin Scale score, mRS 0–2) at 90 days (efficacy). Secondary endpoints include neurological improvement on NIHSS, ordinal mRS shift, Barthel Index, hematoma expansion, and serious adverse events. Blinded assessors will evaluate clinical outcomes, with central adjudication of neuroimaging.

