At baseline, brain non-contrast computed tomography (NCCT) and computed tomography angiography (CTA) scans, demographics, medical history, physical examination, vital signs, clinical scores [NIHSS, premorbid mRS and Barthel index (BI)], and eligibility criteria review will be recorded. The ICF signature will be collected prior to any study-specific procedure. Procedures completed as part of the standard of care but prior to ICF signature may be used for eligibility verification and baseline assessments.

All subjects, regardless of arm assignment, will have laboratory tests collected, and stroke treatment and rehabilitation programs will be implemented at the investigators’ discretion. Throughout the study, concomitant medications and adverse events (AEs) will be collected. Results will be investigator-assessed using Common Terminology Criteria for Adverse Events (CTCAE) version 5.0 (published November 27th, 2017).

Eight-eight subjects will be enrolled at 1:1 ratio.

After randomization, 44 subjects will receive an intravenous infusion of 50 mL cerebrolysin mixed with 250 mL of saline over 30 min once daily from Day 1 to Day 14 (14 consecutive days of treatment) plus standard of care treatment at the discretion of the investigator (treatment arm). The first dose of cerebrolysin must be administered as soon as possible and within 6 h from ICH onset. Another 44 subjects will be subject to receive standard of care treatment alone at the discretion of the investigator (control arm).

All subjects will be scheduled for intensive motor and/or speech and language rehabilitation, as stated in Polish reimbursement guidelines (120 min Per patient in patients with BI≥75 and 180 min Per patient in those with BI<75 day 5 days a week; additionally, all patients undergo 60 min Rehabilitation on Saturdays; in aphasic patients, speech therapy is additionally applied 5 days a week for 30 min).

Cerebrolysin will be administered once daily from Day 1 to Day 14 or until the end of treatment due to death, intolerable adverse events, subject loss to follow-up, consent withdrawal or study termination. Patients who discontinue treatment and receive at least one dose of cerebrolysin will be asked to attend all follow-up visits. A subject is considered as lost to follow-up when all follow-up efforts have been unsuccessful.

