All subjects will undergo neurological assessments conducted by experienced stroke neurologists designated by the investigator: National Institutes of Health Stroke Scale (NIHSS) on Day 1 (at baseline), Day 2, Day 7, Day 14, Day 30, and Day 90; modified Rankin Scale (mRS) and BI on Day 1 (premorbid), Day 30 and Day 90.

The baseline brain NCCT and CTA will be completed on Day 1 (baseline) and the follow-up CT scan on Day 2 (24 ± 4 h from randomization) and day 14 ± 1 right after treatment termination. This will allow to assess the evolution of swelling which also reflects the status of blood–brain barrier permeability. The magnetic resonance imaging (MRI) scan will be completed on Day 90 ± 7 (41).

If on-site neurological assessment is not possible, investigators should schedule a telephone visit and collect information remotely.

Please refer to Table 3 for study schedule details. The trial assessment flowchart is presented in Figure 1.

**Table 3 tab3:** Treatment schedule.

Treatment/procedure	Day 1 (screening)	Day 1 (baseline)	Day 2	Day 7	Day 14	Day 30	Day 90
Informed consent	x						
Eligibility assessment	x						
Demographics	x						
Medical history	x						
Physical examination*	x					x	x
ECOG score	x					x	x
Vital signs**	x					x	x
Pregnancy test, if applicable	x						
CT scan***	x		x		x		
MRI scan							x
mRS		x				x	x
NIHSS		x	x	x	x	x	x
Barthel index		x				x	x
Adverse events	x	x	x	x	x	x	
Concomitant medications	x	x	x	x	x	x	x
Randomization		x					
Cerebrolysin treatment (if allocated)		x	x	x	x		

*Physical examination: assessment of general appearance and review of organ systems (dermatologic, head, eyes, ears, nose, mouth/throat/neck, thyroid, lymph nodes, respiratory, cardiovascular, gastrointestinal, extremities, musculoskeletal, and neurologic systems). **Vital signs: pulse rate, respiratory rate, O2 saturation, body temperature, and blood pressure (systolic/diastolic, subjects should be supine/sitting for 5 min before assessment). ***Baseline brain NCCT and CTA scan on Day 1 (baseline) and follow-up CT scan on Day 2 (24 ± 4 h from randomization), and Day 14 (±1 day from randomization).

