### Adverse events

At the time of study completion or early withdrawal, subjects will be asked directly about any AEs, concomitant medications, and concurrent procedures, which bias will be recorded in the source documentation and CRF. At the final study visit, subjects with ongoing AEs that are considered by the investigator to be study drug-related will be requested to continue to follow-up with the investigator until the AE resolves, stabilizes, or follow-up is no longer possible/necessary. Subjects will continue their prescribed medications and rehabilitation program following study completion. Any serious adverse event (SAE) that occurs while on study must be reported to the sponsor/designee for the study within 24 h after the site becomes aware of the event.

An SAE is defined as any untoward medical occurrence that at any tested drug dose: results in death, is life-threatening, requires hospitalization or prolongs existing hospitalization, results in persistent disability, is a congenital anomaly/birth defect or is medically important.

Medical and scientific judgment must be exercised in determining whether an AE is considered “medically important.”

Hospitalization is defined as (i) admission to a hospital/inpatient facility or (ii) staying at the hospital for treatment or observation for more than 24 h. Events leading to hospitalizations for the following reasons should not be reported as SAEs: (i) trial-related purposes not associated with any deterioration in condition, (ii) precautionary hospitalization for dosing of the study drug without any associated deterioration, (iii) social reasons in the absence of any deterioration in the patient’s general condition, (iv) elective surgery or other scheduled hospitalizations that were planned before the patient was enrolled for this trial.

Good Clinical Practice (GCP), European Medicines Agency pharmacovigilance, and national regulations for reporting adverse drug reactions (ADRs) and suspected unexpected serious adverse events (SUSAR) apply to both arms.

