### Primary objectives

Safety outcome: mortality at day 90.Efficacy outcome: regaining functional independence (mRS 0–2) at Day 90 following stroke onset.

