### Statistical analysis

The study will be analyzed according to the intention-to-treat (ITT) principle. The primary analysis will include all randomized patients regardless of protocol adherence. A secondary per-protocol analysis will include only patients who received at least 80% of the planned cerebrolysin doses in the treatment arm and completed all required assessments.

If the patient’s treatment allocation was disclosed to the outcome adjudicator prior to the assessment, a substitute independent adjudicator will evaluate the patient. Safety analysis will apply to subjects who received at least one dose of cerebrolysin.

Details of the statistical analyses will be provided in the study’s statistical analysis plan (SAP), which will be finalized before enrolling the first patient. Any changes to the methods described in the plan will be described and justified in the final clinical study report.

Data will be summarized using descriptive statistics with 95% confidence intervals (CIs) where applicable. For continuous variables, the number of subjects, mean, standard deviation, median, minimum, and maximum values will be reported. Frequencies and percentages will be used to summarize categorical variables. Results will be presented as proportions or adjusted odds ratios with 95% confidence intervals and corresponding *p*-values. Analyses will be adjusted for the stratification factors (baseline ICH volume and GCS score). Missing data will be handled using multiple imputation methods for the primary and key secondary endpoints, with sensitivity analyses performed using alternative approaches (last observation carried forward, worst-case imputation) to assess the robustness of findings. A tipping-point analysis will be conducted for the primary endpoint to determine the impact of missing data on the final conclusions.

The following subgroup analyses are pre-specified according to age (≤65 vs. >65 years), baseline ICH volume (30–50 mL vs. 51–80 mL), the time from symptom onset to treatment (≤3 vs. >3–6 h), baseline GCS score (8–12 vs. 13–15).

All AEs and SAEs will be summarized, including the number of events, number of subjects, and percentage of subjects reporting these events, tabulated by preferred term from MedDRA Dictionary. Events will also be summarized by severity and by relationship to the study drug.

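### The safety set is defined by receipt of cerebrolysin, so as written it excludes the control arm from AE/SAE analyses and leaves the set for Day-90 mortality unclear

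*Protocol article*

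**What the plan says.** Two rules on analysis sets stand in the Statistical analysis section. For efficacy and the trial as a whole, the intention-to-treat principle applies: "The primary analysis will include all randomized patients regardless of protocol adherence". For safety: "Safety analysis will apply to subjects who received at least one dose of cerebrolysin".

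The control arm is described under Intervention: "Another 44 subjects will be subject to receive standard of care treatment alone at the discretion of the investigator (control arm". There is no placebo.

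Day-90 mortality is named twice. Primary objectives has "Safety outcome: mortality at day 90", and the abstract's Methods has "Primary endpoints include 90-day mortality (safety) and functional independence (modified Rankin Scale score, mRS 0–2) at 90 days (efficacy". Secondary objectives adds SAEs up to Day 30 as an endpoint.

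On the collection of adverse events, Intervention says "Throughout the study, concomitant medications and adverse events (AEs) will be collected", and the Adverse events section says "At the time of study completion or early withdrawal, subjects will be asked directly about any AEs". In Table 3 the row "Adverse events" is marked at screening, baseline and Days 2, 7, 14 and 30, and is blank at Day 90.

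**The concern.** Restricting the safety set to patients who took the drug is a familiar convention. It works when both arms receive a study product, active or placebo. Here the control arm receives none, so the same wording removes that arm altogether.

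The consequence matters in this population. Patients enter with haematomas of 30–80 mL and an NIHSS of at least 8, so serious events from the haemorrhage itself are to be expected. An SAE rate in treated patients alone cannot separate harm from the drug from the course of the disease; only the randomised comparison can. Safety is part of the study objective, and Limitations and strengths makes a larger trial depend partly on its being confirmed.

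The wording also touches a primary endpoint. Because Day-90 mortality carries the label of safety outcome, a reader of the Statistical analysis section can assign it to either set. Under the dosed-only rule there would be no control deaths, and a patient allocated to cerebrolysin who died before the first infusion would not be counted either.

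**Working it through.** The question is mainly one of setting the sections side by side. The arithmetic is short.

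1. **The plan's own figure.** Study design and settings bases the sample size on survival of 59.4% against 27.8% in an earlier trial, an absolute difference of 30 points, alpha 0.05 and 80% power (the text gives 0.80 as beta; read here as power). With p1 = 0.278, p2 = 0.578, mean 0.428, two-sided alpha and pooled variance:

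   n = [1.960 × √(2 × 0.428 × 0.572) + 0.842 × √(0.278 × 0.722 + 0.578 × 0.422)]² / 0.30²
   = [1.371 + 0.561]² / 0.09 ≈ 41.5, so 42 per arm.

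   Then 84 × 1.05 = 88.2, or 88. The stated figure is reproduced. It is a between-arm comparison of survival, so the plan intends mortality to be compared across arms.

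2. **Who is in the safety set.** Inputs from Intervention: 44 patients allocated to cerebrolysin plus standard care, 44 to standard care alone. The entry condition is one dose or more of cerebrolysin. Controls treated as allocated: 0 of 44 qualify. The set therefore holds at most 44 of 88 patients, and 44/88 = 50% are excluded.

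3. **What that set can estimate.** As an illustration only, take mortality of 1 − 0.594 = 40.6%, the treated-arm value implied by the reference trial at 6 months. In 44 treated patients the 95% half-width is 1.96 × √(0.406 × 0.594 / 44) = 0.145. The output is a single proportion of about 41% ± 14.5 points, with no difference, risk ratio or odds ratio against control. The same holds for any AE or SAE rate from this set.

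4. **Whether control data exist.** Under Intervention, the paragraph that calls for AE collection opens by covering all subjects whichever arm they are in. In Table 3 only the cerebrolysin row is qualified by allocation. The Adverse events section applies the reporting rules for adverse reactions to both arms. So the data for a comparison are collected, and the set definition leaves them out.

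5. **Which rule governs Day-90 mortality.**
   - As a primary endpoint (abstract, Primary objectives), it falls under the all-randomised rule.
   - As the outcome labelled safety (same places), it falls under the dosed-only rule.
   - No sentence in the article says which takes precedence.

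6. **Table 3 against the text.** The AE row has six marks and ends at Day 30. The next row, concomitant medications, has seven and includes Day 90, so the gap is unlikely to be lost formatting. The text requires collection during the whole study and direct questioning at its completion, and Day 90 is the last scheduled visit. A site following the table and a site following the text would collect different non-fatal events between Day 30 and Day 90.

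**The case against.** The strongest reply is that the plan as a whole clearly intends a comparison. Mortality is a primary endpoint, the primary analysis takes in everyone randomised, the sample size rests on a survival difference between arms, and the Sample size section speaks of confirming a mortality effect. The paragraph on AE and SAE summaries in Statistical analysis is not itself limited to treated patients. An analysis plan exists or will exist and could set this right.

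Much of this stands, and it rules out several stronger readings:

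- A reader might infer that the primary safety outcome has no control arm. The article does not support that. The all-randomised sentence can supply the arm, so what remains is an unresolved conflict between two rules.
- A reader might infer from Table 3 that the Day-90 safety endpoint goes unrecorded. It does not. That endpoint is death, which the Day-90 visit, the mRS and the 24-hour SAE reporting duty all capture. The SAE endpoint itself stops at Day 30, where the table's last mark stands.
- A reader might go on to argue that safety cannot be confirmed because a between-arm mortality difference would have a 95% half-width near 20 points (for example 1.96 × √(0.406 × 0.594 / 44 + 0.722 × 0.278 / 44) = 0.196). That width comes from 88 patients, is acknowledged as a limitation of small size, and would be the same after the correction. It is no part of this point.

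What does not stand is the appeal to the analysis plan. The sentence on the safety set is a rule already fixed in the article, not a detail left open, and an analysis plan that follows it would carry the fault forward.

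**Conclusion.** The safety-set rule is wrong as written. Followed literally, it removes 44 of 88 patients from AE and SAE analyses built on it and leaves the secondary SAE endpoint without a comparator, although the control data are collected. This conclusion assumes only that controls are treated as allocated.

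For Day-90 mortality the finding is narrower: two rules in one section could apply, and the article does not choose between them. The design points to the all-randomised set, but the text should say so.

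The blank Day-90 cell in Table 3 is a real but minor inconsistency. It concerns non-fatal events after Day 30 and threatens neither the mortality endpoint nor the Day-30 SAE endpoint. The sample size is unaffected.

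**What to change.** Replace the safety-set sentence with wording to this effect:

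> *The safety set comprises all randomised patients in both arms, grouped by treatment received: cerebrolysin if one or more doses were given, otherwise standard care. AEs and SAEs, including SAEs to Day 30, are tabulated by arm with the between-arm difference and its 95% CI. Day-90 mortality is analysed in all randomised patients as allocated.*

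A patient allocated to cerebrolysin but never dosed would then count with standard care in the AE tables and with the cerebrolysin arm for mortality. Report the number of such patients, so that the two presentations can be read together.

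Reconcile the Day-90 cell of the adverse-event row in Table 3 with the Intervention and Adverse events sections, so that all sites collect events over the same period.

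The cost is a few sentences in the protocol, matching text in the analysis plan, and one table cell. The control patients and the Day-90 visit are already in the design; no extra patients or visits are needed.

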### Participants

The study participants will be patients with acute ICH in whom allocated treatment can be initiated within 6 h of stroke onset and in whom a clinically meaningful benefit from treatment is considered possible. The full eligibility criteria are listed in Table 1.

**Table 1 tab1:** Inclusion and exclusion criteria.

Inclusion criteria	Exclusion criteria
1. Age 18–80 years	1. Hemorrhage caused by head trauma
2. NIHSS ≥8 at randomization	2. Medical history or neuroimaging findings suggestive of ruptured aneurysm, arteriovenous malformation (AVM), vascular anomaly, Moyamoya disease, venous sinus thrombosis, mass or tumor, hemorrhagic transformation of an ischemic infarct
3. Time from stroke onset <6h*	3. Intraventricular extension of the hemorrhage visually involving >50% of either of the lateral ventricles
4. Pre-randomization head CT demonstrating an acute, primary lobar ICH	4. Thalamic and basal ganglia ICH
5. ICH volume 30–80 mL	5. Infratentorial parenchymal hemorrhage, including midbrain, pons or cerebellum
6. Glasgow Coma Score (GCS) 8–15	6. Current use of low molecular weight heparins in therapeutic dose
7. No history of prior stroke	7. Uncorrected coagulopathy or known clotting disorder
8. Pre-stroke independence (modified Rankin Score 0–2)	8. Platelet count < 75,000, International Normalized Ratio (INR) > 1.4 after correction
9. Ability to provide informed consent	9. End stage renal disease
	10. Patients with a mechanical heart valve
	11. End-stage liver disease
	12. Epilepsy with grand mal seizure
	13. History of drug or alcohol use or dependence that, in the opinion of the site investigator, would interfere with adherence to study requirements
	14. Positive urine or serum pregnancy test in female subjects without documented history of surgical sterilization or post-menopausal
	15. Known life-expectancy of less than 6 months
	16. No reasonable expectation of recovery, Do-Not-Resuscitate (DNR), or comfort measures only prior to randomization
	17. Participation in a concurrent interventional medical investigation or clinical trial
	18. Inability or unwillingness of subject or legal guardian/representative to give written informed consent
	19. Any condition that would represent a contraindication for cerebrolysin administration

*Cerebrolysin treatment can be initiated within 6 h after the onset of stroke. If the actual time of onset is unclear, the time the subject was last known to be well will be used instead.

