### Allocation

Participants will be stratified according to baseline ICH volume (30–50 mL vs. 51–80 mL) and Glasgow Coma Scale score (8–12 vs. 13–15) using randomised permuted blocks (block size 4) in a 1:1 ratio. Randomization will occur after baseline assessment using a computer-generated random allocation sequence. The treatment assignment will be provided to the site once a subject meets all eligibility criteria. The randomizing physician will be blinded to allocated treatment prior to randomization. Blocking details will be included in the Randomization Plan managed by the sponsor and will be unavailable to investigators enrolling participants and assigning interventions.

Subjects, healthcare providers, and data collectors will be aware of treatment allocation, while the independent outcome adjudicator will remain blinded.

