### Secondary objectives

Neurological improvement from the deficit at baseline measured by NIHSS at Day 2, 7, 30, and 90.Ordinal shift analysis of mRS at Day 90.Improvement in activities of daily living from the status at baseline measured by BartheI Index on Day 30 and 90.Avoiding hematoma growth from Day 1 to Day 2, defined as both absolute (>12.5 mL) and relative (>35%) increases in hematoma volume measured using semi-automated volumetric analysis on NCCT.Absolute hematoma size shift.SAE until day 30.

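### The named adjustment set leaves out baseline NIHSS and age, both already collected; prespecifying them would bring a modest gain in efficiency

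*Protocol article*

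**What the plan says.** The Statistical analysis section of the protocol article fixes the covariates in one sentence: "Analyses will be adjusted for the stratification factors (baseline ICH volume and GCS score"). No further covariate is named there or elsewhere. The Allocation section defines the two factors for randomization: "Participants will be stratified according to baseline ICH volume (30–50 mL vs. 51–80 mL) and Glasgow Coma Scale score (8–12 vs. 13–15").

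Both of the other variables are available. The Intervention section lists among the baseline records "demographics, medical history, physical examination, vital signs, clinical scores [NIHSS, premorbid mRS and Barthel index (BI"). Table 1 makes both of them entry criteria, "NIHSS ≥8 at randomization" and "Age 18–80 years", so neither should be missing in an eligible patient. Age returns in the analysis text as a subgroup factor: "The following subgroup analyses are pre-specified according to age (≤65 vs. >65 years").

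The first secondary objective is "Neurological improvement from the deficit at baseline measured by NIHSS at Day 2, 7, 30, and 90". The article gives no model for it. It leaves analysis details to a SAP that is to be final before the first enrolment and is not available here.

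**The concern.** The trial is small, and its two primary endpoints are binary (death by Day 90; mRS 0–2 at Day 90). In that setting a prognostic baseline covariate named in advance can add power at almost no cost. Age spans 18 to 80 years and NIHSS has no upper limit at entry, so both can vary widely within the randomization strata. Stratifying on GCS and volume balances them only as far as they correlate with those factors.

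For NIHSS outcomes the question is more specific. If improvement is analysed as follow-up minus baseline, with volume and GCS as the covariates, baseline NIHSS enters only through the subtraction. That is usually less efficient than using it as a covariate. It matters here because the Sample size section says the trial should supply means and standard deviations for planning a larger one.

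There is also a point of credibility. If the arms turn out to differ on NIHSS or age, a covariate added at that stage looks data-driven. Naming it beforehand avoids this.

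**Working it through.** **1. The plan's own figure.** The inputs, from Study design and settings, are survival of 27.8% in the earlier trial's control arm, an absolute difference of 30 points, alpha 0.05 (taken as two-sided) and beta 0.80 (read as power 0.80). With pooled variance and no continuity correction:

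n per arm = [1.96·√(2·p̄·q̄) + 0.8416·√(p₁q₁ + p₂q₂)]² / (p₂ − p₁)²

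With p₁ = 0.278, p₂ = 0.578 and p̄ = 0.428, this is [1.3715 + 0.5612]² / 0.09 = 41.5, so 42 per arm. Then 84 × 1.05 = 88.2, which agrees with the stated 88. This is an unadjusted formula and takes no credit for covariates. Unadjusted power at 44 per arm is 0.823.

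**2. Primary survival comparison with and without the two covariates.** The documents give no prognostic strengths, so these were assumed. The set-up was logistic regression with n = 88, treatment balanced within the four strata, survival of 27.8% vs 57.8%, a log-odds of 0.7 for each stratification factor, an NIHSS–GCS correlation of 0.3 or 0.6, no loss to follow-up, and 3000 runs per scenario. In each cell the first figure is power with the two stratification factors; the second is power with NIHSS and age added.

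| Log-odds per SD, NIHSS / age | Correlation 0.3 | Correlation 0.6 | Equivalent extra patients |
|---|---|---|---|
| 0 / 0 (none) | 0.857 → 0.853 | 0.845 → 0.845 | about 0% |
| 0.3 / 0.3 (weak) | 0.839 → 0.848 | 0.849 → 0.858 | about 3% |
| 0.6 / 0.4 (moderate) | 0.838 → 0.864 | 0.864 → 0.888 | about 8% |
| 0.9 / 0.6 (strong) | 0.839 → 0.888 | 0.866 → 0.913 | 16–17% |

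The last column is [(1.96 + z_new)/(1.96 + z_old)]² − 1. For 0.838 → 0.864 this is (3.058/2.946)² − 1 = 0.08. Type I error was 0.044 to 0.059 across both covariate sets, and adding the two terms moved it by at most 0.003. The Monte Carlo standard error of one power figure is √(0.85 × 0.15/3000) = 0.0065. Both models were fitted to the same simulated data, so the differences are steadier than that.

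**3. mRS 0–2.** The documents give no planning rates. With assumed rates of 15% vs 35% and correlation 0.5, power went from 0.601 to 0.596 (none), 0.621 to 0.644 (moderate) and 0.620 to 0.674 (strong). The ordinal mRS model was not simulated.

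**4. NIHSS as a continuous outcome.** Let r be the baseline to follow-up correlation and k the ratio of baseline SD to follow-up SD. The variance of a baseline-adjusted comparison relative to a change-score comparison is

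(1 − r²) / (1 + k² − 2rk)

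With k = 1 this reduces to (1 + r)/2, which is 0.65, 0.75 and 0.85 for r = 0.3, 0.5 and 0.7. The reciprocals are 1.54, 1.33 and 1.18. With k = r the denominator becomes 1 − r², the ratio is 1 and the gain is nil. For r = 0.5, the variance saving therefore falls from 25% at k = 1 to zero at k = 0.5. Entry at NIHSS 8 or more truncates the baseline distribution and not the follow-up, so k may well be below 1. GCS and volume already explain part of the outcome, and deaths leave some patients without a Day 90 score. The k = 1 figures are therefore not estimates for this trial.

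**The case against.** The strongest reply is that nothing here is wrong. Adjusting for the stratification factors matches the randomization, the planned 88 reproduces without any covariate, and further covariates are ordinary SAP content. All of that stands, so this is an improvement to a stated choice and not the correction of an error. The point remains worth raising because the article does name an adjustment set, and two obvious candidates are not in it.

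Several stronger readings are tempting, and the documents do not support them:

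- **That other covariates are excluded.** The sentence names two factors and does not say they are the only ones. The SAP may add more.
- **That NIHSS will be analysed as a change score.** The objective speaks of improvement from baseline but gives no estimator. A baseline-adjusted model or a proportion improved would fit it equally well, and the section reports results as proportions or adjusted odds ratios. A gain of 18–54% more patients, from 1/0.85 and 1/0.65, would need the change score, equal variances and the assumed correlations together.
- **That volume and GCS are dichotomised in the models.** The cut-points belong to the randomization and the subgroups. The adjustment sentence does not say how the factors enter.
- **That precision of the primary odds ratio is lost.** In logistic regression, adding a prognostic covariate does not shrink the standard error of the log odds ratio. The gain is power for the conditional effect.
- **That chance imbalance invalidates the primary result.** With 44 per arm, a standardised difference in an unstratified covariate has a standard error of √(2/44) = 0.21, so a difference above 0.2 SD arises about 35% of the time (less often for NIHSS as far as GCS balances it). The test already allows for this, as the type I error figures show.

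**Conclusion.** The point holds as a modest efficiency gain. The stated analysis is valid and does not put the trial below its planned 80% power. Prespecifying baseline NIHSS and age would change power for survival by about 0 to 5 points, about 2.5 if their prognostic strength is moderate and nothing if they carry none. That range rests on assumed prognostic strengths, an assumed NIHSS–GCS correlation and the planning survival rates, which come from 6-month data in an earlier trial although the endpoint here is at 90 days. For mRS 0–2, under further assumed event rates, the change ranged from a loss of half a point to a gain of just over 5 points. For NIHSS outcomes a precision gain follows only if a simple change from baseline would otherwise be used. Its size depends on the correlation and on the ratio of the variances, neither of which the documents give.

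**What to change.** Extend the adjustment sentence in the Statistical analysis section, or confirm that the SAP already does so, along these lines: *The mortality, mRS 0–2 and ordinal mRS models will adjust for baseline ICH volume, GCS, age and baseline NIHSS, with age and NIHSS as continuous terms. NIHSS outcomes at each visit will adjust for baseline NIHSS in addition to ICH volume and GCS.* This should be settled before the first patient is enrolled, as the article already promises for the SAP.

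No new data or visits are needed. The cost is two more terms in the binary and ordinal models. At the assumed mRS 0–2 rates, 44 × 0.15 + 44 × 0.35 = 22 events are expected. That is 22/5 = 4.4 events per term (treatment, volume, GCS, age, NIHSS), against 22/3 = 7.3 with the present set. If events are that few, a penalised (Firth) fit may be needed, and the condition for using it should be written down in advance. In the simulations at these rates, at most 0.2% of fits failed under either covariate set.
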